#### Sample size consideration

Due to this study being a feasibility and acceptability study, formal sample size calculations were not undertaken. During the 28-month recruitment period of this study (from November 2023 to March 2026), it is estimated that approximately 17 groups will be offered across three NHS trusts (with ideally 4–8 participants in each group). Therefore, the potential pool of participants is 64 to 128 participants. It is planned to recruit 50% of this potential pool of participants (*n* = 32), approximately ten to 11 participants per site for baseline recruitment. This sample size reflects the median target baseline recruitment rate of 30 participants for feasibility studies in the United Kingdom (UK) (43). As an important part of the overall study aims to assess the feasibility of recruitment and retention, possible dropouts have not been factored into this calculation.

Retention of participants in the study will be examined using Lewis et al.’s (44) framework for assessing retention as a progression criterion. By applying the ‘traffic light system’, a retention rate above 85% will be considered acceptable (GREEN), 65% to 84% will be considered a borderline level of retention (AMBER), and below 65% (RED) will be deemed as a low level of retention. For any future studies on P-CFT in NHS perinatal services, a GREEN retention rate will indicate that the current study methodology is feasible for participant recruitment. Several amendments may be required to the methodology following an AMBER retention rate. A retention rate of RED demonstrates that considerable changes would be necessary to improve retention of participant recruitment. A preliminary exploration of attrition bias will also be conducted to examine if certain demographics or variables may influence attrition (e.g., number of children, financial situation).

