Since Millard and Wittkowski’s (21) review, another two evaluations of P-CFT groups in P-CMHTs were published: in both evaluations, service users experienced more moderate to severe PMH difficulties (27, 28). Service users presenting with a wide range of mental health difficulties were included, such as anxiety, posttraumatic stress disorder (PTSD), complex PTSD or birth trauma, obsessive compulsive disorder (OCD), personality disorders, and eating disorders. Both evaluations reported significant improvements across compassion-based outcomes, mood, and postpartum bonding, but no control groups were implemented. Although these two evaluations provided an insight into the potential benefits of P-CFT, the data were extracted retrospectively from self-reported outcomes in electronic health records. It is unclear from these evaluations if a further exploration into P-CFT is feasible in an NHS perinatal service. Given the limitations of the above-mentioned studies, a study using a stronger methodological rigour is required to explore the potential benefits of P-CFT. However, prior to a large-scale efficacy study, further exploratory studies are warranted (29). This multisite study aims to explore the feasibility and acceptability of the P-CFT groups based on Cree (10, 11) and the study design in perinatal mothers and birthing parents through three components. More specifically, the objectives are as follows:

to explore the feasibility of the study design through recruitment and retention rates and quality of data collection (Component 1, Component 2),to determine the suitability of the outcomes and their respective measures (Component 1),to assess the acceptability of the intervention through a qualitative process evaluation to identify factors associated with engagement and adherence to P-CFT (Component 3),to conduct an exploration of P-CFT has on compassion-based outcomes (i.e., self-compassion, self-criticism), psychological well-being and parent-infant interactions (Component 1, Component 2, Component 3).

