### Design

The study will adopt a single pre-post, quasi-experimental study design comprising three components (in this protocol, these components are referred to as Component 1, 2 and 3). This study design provides a convergent-parallel mixed methods process evaluation (30), which encapsulates the assessment of feasibility and acceptability, required as part of the MRC *Framework for Developing and Evaluating Complex Interventions* (29). The convergent-parallel approach entails the collection and analysis of quantitative and qualitative data, which are subsequently integrated and compared to allow for a unified analysis (30). Data from Components 1 and 2 will use quantitative methods and Component 3 will generate qualitative data. **Figure 1** displays an overview of the study design that reflects CONSORT guidelines (31), wherein a schedule of the study enrolment and assessments are provided in **Table 1**.

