### Component 1: feasibility study

#### Design

This component will use a non-randomised longitudinal, repeated measures design, across three research sites through routinely collected data and self-report outcome measures.

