#### Participant inclusion/exclusion criteria

Mothers and birthing parents are first referred to and assessed by the P-CMHT to determine their suitability for the service. If they meet the service criteria, they can be referred to the P-CFT group. Once enrolled to receive P-CFT and consent-to-contact is provided, the research team will assess a service user’s eligibility against the study criteria. To participate in the study, it is required that mothers^1^ are at least 18 years of age and have a baby that is less than two years old at the time of starting the P-CFT group OR they are currently pregnant and can complete the intervention prior to approximately 34 weeks gestation. Participants are excluded from the study if they are not receiving care from a P-CMHT, deemed unsuitable by the P-CMHT to receive a group intervention, assessed as acutely at risk of harm to their baby, experiencing acute psychotic symptoms, alcohol or substance misuse, active suicidality and/or lacking capacity to consent under the Mental Capacity Act 2005 (41).

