#### Data analysis of secondary outcomes

Summary statistics of the included measures (FCS-SC, SOCS, PBQ, CORE-10, DASS-21, SWEMWBS, CORE-10) at each timepoint will be presented in tables and/or graphs. Exploratory analyses of these outcomes will be conducted using the appropriate statistical method. The effect sizes generated from the secondary clinical outcomes, particularly the compassion-based measures, will also help to inform power analyses for larger scale definitive trials of P-CFT. To assess the effects of P-CFT at an individual-level, Jacobson and Truax’s (58) reliable change index will be utilised. For each measure, the percentage of participants that report a clinically significant change from Time 1 to Time 2 and Time 3 will be reported.

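### A GREEN retention rate among women who all receive P-CFT is read as showing feasible recruitment for any later P-CFT study, which is broader than retention in an uncontrolled cohort can support

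*Protocol article*

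**What the plan says.** All references are to the Protocol article.

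- **The rule.** *Sample size consideration* (Component 1) treats retention as a progression criterion: above 85% is GREEN, 65% to 84% AMBER, below 65% RED. It then says: "For any future studies on P-CFT in NHS perinatal services, a GREEN retention rate will indicate that the current study methodology is feasible". The sentence closes by naming recruitment of participants as the thing shown to be feasible. No other feasibility outcome has thresholds.
- **The design.** The main *Design* section says: "The study will adopt a single pre-post, quasi-experimental study design comprising three components". The *Design* section of Component 1 says: "This component will use a non-randomised longitudinal, repeated measures design". There is no comparison group.
- **Who is approached.** Under *Participant inclusion/exclusion criteria*, study eligibility is assessed "Once enrolled to receive P-CFT and consent-to-contact is provided".
- **How retention is counted.** *Primary feasibility and acceptability outcomes* defines it as the consented participants still in Component 1 at post-intervention and at follow-up. The same section separately records how many eligible patients consent and how many decline. *Data analysis of primary outcomes* adds counts of referrals, consents to contact and informed consents.
- **What is to follow.** The *Introduction* notes that two earlier evaluations had no control groups and says that "prior to a large-scale efficacy study, further exploratory studies are warranted". *Data analysis of secondary outcomes* says that the effect sizes "will also help to inform power analyses for larger scale definitive trials of P-CFT".

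**The concern.** A progression rule should conclude only on what its data measure. This one goes too far in two ways.

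1. **From retention to recruitment.** Retention is conditional on having consented. Women who decline are in neither the numerator nor the denominator, so the rate cannot show whether recruitment works.
2. **From this cohort to any later P-CFT study.** Every participant was already due to receive P-CFT. Joining the study did not put her place at risk, and no one is followed without the therapy. Retention in a comparison group is not observed. Yet the protocol itself names the lack of control groups as a limitation of earlier work and looks ahead to an efficacy study and definitive trials.

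What is at stake is how the result will be cited. A reader planning a later study could take a GREEN result as support for recruitment, or for follow-up in a controlled comparison, when neither was tested by the graded quantity.

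**Working it through.** **Inputs** (Protocol article, *Sample size consideration*, Component 1): pool 64 to 128; planned recruitment 50%, n = 32; GREEN above 85%. There are no power inputs to check, since "formal sample size calculations were not undertaken".

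**Step 1. Reproduce the planned n.** 0.50 × 64 = 32, so the plan's figure follows from the lower end of its pool.

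**Step 2. Smallest GREEN result at n = 32.** 27/32 = 84.4%, not above 85%. 28/32 = 87.5%, GREEN. So GREEN means at least 28 of 32 retained.

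**Step 3. Precision of that result.** The exact (Clopper-Pearson) 95% limits for 28/32 are the 2.5% quantile of Beta(28, 5) and the 97.5% quantile of Beta(29, 4): 71.0% to 96.5%. A result that is just GREEN is compatible with true retention well inside the AMBER band.

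**Step 4. What the colour depends on.** With X the number retained and p the true retention among consented women receiving P-CFT, P(GREEN) = P(X ≥ 28), where X is binomial(32, p).

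| True retention p | P(GREEN) |
|---|---|
| 80% | 0.204 |
| 85% | 0.464 |
| 90% | 0.789 |
| 95% | 0.980 |

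Only n and p enter. The consent rate does not appear, and nor does retention in any group without P-CFT.

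**Step 5. The colour cannot tell good recruitment from poor.** Use the two ends of the plan's own pool and hold the outcome at 28 of 32 retained.

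| Pool | Recruited | Recruitment rate | Retention | Colour |
|---|---|---|---|---|
| 64 | 32 | 32/64 = 50% | 28/32 = 87.5% | GREEN |
| 128 | 32 | 32/128 = 25% | 28/32 = 87.5% | GREEN |

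The recruitment rate halves and the colour does not change.

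**Step 6. Comparison-group retention.** The protocol gives no figure for it and specifies no comparator, so no size can be put on the difference from documents alone. The point is structural: the cohort contains no one whose follow-up would estimate it.

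**The case against.** The strongest reply is that the sentence is already limited. It speaks of the current methodology, which is uncontrolled repeated follow-up, and AMBER and RED lead only to changes in that methodology. Recruitment is also assessed apart from the colour, through consents, declines and referral counts, and the *Discussion* says that barriers to recruitment will be explored. A single-arm feasibility study is a legitimate choice, and none of the four objectives promises to test randomisation.

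Most of this stands. It rules out three stronger readings that a reader might infer:

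- **That GREEN clears a randomised trial.** No section ties a colour to a decision to start an efficacy trial, and none says that the next study will be definitive or randomised. The *Introduction* speaks of further exploratory studies first, so a pilot with a comparator could come between. That a controlled study will follow at some stage is a fair inference from the remark about control groups, but it is not a stated plan.
- **That willingness to be randomised is never asked about.** The listed interview themes (referral, content and delivery, benefit) do not mention it. But neither the full topic guide nor the full questionnaire is shown, so the absence of any such prompt or item cannot be established.
- **That comparison-group retention would be lower by some amount.** Any such figure would be pure assumption. Even the direction depends on a comparator that is not specified.

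The reply does not rescue the sentence itself. Limiting the object to the current methodology still leaves the scope as every later P-CFT study in these services, and still draws a recruitment conclusion from a retention rate. That recruitment counts are collected elsewhere is a reason to use them, not a reason to let retention stand in for them.

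**Conclusion.** The point holds as one of scope. As written, GREEN is said to show something about recruitment, and about any future P-CFT study in NHS perinatal services. The data behind it can show only that consented women who all receive P-CFT can be kept in repeated self-report follow-up. The design itself is not at fault.

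The size that can be stated from the documents is this: the smallest GREEN, 28/32, carries an interval of 71.0% to 96.5%, and the colour is identical at recruitment of 50% or 25% of the pool. These figures assume that exactly 32 are recruited. The interval and the probabilities also treat participants as independent; as P-CFT is delivered in groups, any within-group correlation in dropout would normally widen the interval. The conclusion on scope depends on none of these assumptions. It rests on who is counted in the retention rate.

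**What to change.** 1. **Reword the GREEN sentence** in *Sample size consideration* (Component 1). Suggested text: *A GREEN rate supports the feasibility of retaining women who all receive P-CFT in repeated self-report follow-up. It is not evidence on recruitment, or on retention in a controlled comparison.* Separate recruitment from retention in the RED sentence too, which runs the two together.
2. **Judge recruitment from the recruitment data**: the consent and decline counts in *Primary feasibility and acceptability outcomes*, and the referral and consent counts in *Data analysis of primary outcomes*. Nothing new has to be collected.
3. **Report the retention percentage with its 95% interval beside the colour**, at each timepoint where retention is reported.
4. **Optional:** an interview prompt on how acceptable a comparison group would be. This is a choice of scope, not a correction. A question put only at post-intervention would reach only women who had stayed in the study and had already been offered the therapy, so it would say little about consent at entry.

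Items 1 to 3 cost one or two sentences and one extra figure per timepoint. They need no change to data collection, so they remain possible however far recruitment has advanced. The downside is that a GREEN result will support a narrower claim.

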#### Primary feasibility and acceptability outcomes

Data will be collected to indicate levels of feasibility and acceptability. Retention rates of participants in the study will be examined, which will be the number of consented participants who remain in Component 1 at post-intervention and follow-up. The number of eligible patients who consent to participate in the study as well as the number of patients who decline to participate will also be recorded to assess the feasibility of recruitment strategies. To assess the feasibility of the P-CFT intervention, the attendance of the group sessions will be collected. In addition, the rate of completion of the self-reported outcome measures across each time point will be used to signify their feasibility and acceptability.

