## Discussion

To the authors’ knowledge, this study will be the first multi-site feasibility and acceptability study of perinatal CFT in specialist perinatal mental health services in NHS England. In general, the study will be able to explore and report if an online delivery of this intervention is beneficial for mothers and birthing parents in a specialist perinatal community mental health team. Specifically, the findings can help identify how the content and/or delivery can be adapted to optimise outcomes for P-CFT attendees. For instance, data collection of attendance levels per session will enable an objective measure of acceptability. An increase in attrition may indicate low acceptability of the content of one of the sessions. Possible observations such as this will be able to be further explored qualitatively. Moreover, service users within these perinatal clinical settings present with a range of mental health difficulties. Through the qualitative data collection, the suitability of P-CFT can be explored trans-diagnostically, allowing for further refinement of service delivery.

The suitability of recruitment methods can also be established to identify the type of recruitment methods that are appropriate for this specific type of intervention and clinical setting. Any potential barriers will be noted. For instance, one question is whether or not the recruitment strategies enable a sufficient sample size to be collected. Exploring potential barriers to recruitment and retention will highlight the type of practical issues that may need to be addressed when conducting any futures studies on P-CFT within a specialist perinatal mental health team for both service-users, staff members, and researchers.

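### The only stated progression rule draws a recruitment conclusion from a GREEN retention rate, which carries no information on recruitment

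*Protocol article*

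**What the plan says.** Under Component 1, Sample size consideration, the protocol article adopts a published "framework for assessing retention as a progression criterion". Retention above 85% is GREEN, 65% to 84% is AMBER and below 65% is RED. The conclusions attached to the colours are:

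- GREEN: "a GREEN retention rate will indicate that the current study methodology is feasible for participant recruitment".
- AMBER: several amendments to the methodology may be needed.
- RED: "considerable changes would be necessary to improve retention of participant recruitment".

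The section Primary feasibility and acceptability outcomes defines retention as the consented participants who are still in Component 1 at post-intervention and at follow-up.

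Elsewhere the article treats recruitment as its own question. The first objective in the Introduction is "to explore the feasibility of the study design through recruitment and retention rates and quality of data collection". The Abstract lists feasibility of recruitment first among the aims. Primary feasibility and acceptability outcomes adds, alongside the count of those who consent, that "the number of patients who decline to participate will also be recorded to assess the feasibility of recruitment strategies". The Discussion says that "one question is whether or not the recruitment strategies enable a sufficient sample size to be collected".

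The planned baseline recruitment is 32. No cut-off or colour is tied to that number or to the consent rate.

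**The concern.** Retention is conditional on having been recruited. It shows whether those who joined stayed, and it cannot show whether enough people joined. The GREEN sentence nevertheless uses it to answer the recruitment question, which the article elsewhere separates from retention and for which it collects separate data.

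What is at stake is the message passed to later studies of P-CFT in NHS perinatal services, which the rule is expressly meant to inform. Applied as written, the rule can attach a favourable recruitment label to a study that recruited far below plan. The label concerns the first aim named in the Abstract and comes from the only formal criterion in the article.

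**Working it through.** **Inputs** (all from the protocol article)

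- Planned recruitment: 32, about 10 to 11 per site (Sample size consideration).
- Potential pool: 64 to 128 (same section).
- GREEN: retention above 85%. RED: below 65% (same section).
- Retention denominator: consented participants (Primary feasibility and acceptability outcomes).

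**Step 1: the plan's own figure.** 0.50 × 64 = 32, and 32 / 3 = 10.7 per site. The target of 32 is reproduced from the lower end of the stated pool.

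**Step 2: what the rule depends on.** Let *e* be the eligible service users approached, *c* those who consent and *k* those who remain.

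- Retention = *k* / *c*
- Uptake = *c* / *e*
- Share of target = *c* / 32

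The rule is GREEN when *k* / *c* > 0.85. Neither *e* nor the target of 32 appears in it. For any *c*, however small, *k* = *c* gives 100% and GREEN.

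**Step 3: illustrations.** The counts are chosen to show how the rule behaves and are not forecasts. *k* is taken at whichever time point the rule is applied.

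| Consented | Remain | Retention | Colour | Share of the planned 32 |
|---|---|---|---|---|
| 5 | 5 | 100% | GREEN | 5/32 = 15.6% |
| 10 | 9 | 90% | GREEN | 10/32 = 31% |
| 32 | 28 | 87.5% | GREEN | 100% |
| 32 | 20 | 62.5% | RED | 100% |

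In the second row, 10 consents are 10/64 = 15.6% to 10/128 = 7.8% of the stated pool. The article's 17 groups of 4 to 8 would give a pool of 68 to 136 instead. The share is then 10/68 = 14.7% to 10/136 = 7.4%, and the point is unchanged.

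**Step 4: what each colour concludes.** The first three rows are all GREEN and so all receive the same statement that the methodology is feasible for recruitment, although recruitment ranges from 15.6% to 100% of plan. The fourth row is RED. The text then calls for changes to improve retention, which is apt when 12 of 32 have been lost, and it does not say that recruitment failed. The false inference is therefore confined to GREEN.

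**The case against.** **It is probably a slip of the pen.** The paragraph around the sentence is about retention: the framework, the three bands and the attrition analysis that follows. The RED phrase reads like a garbled reference to keeping recruited participants. This may well be right. But it is the published reading of the only progression rule, and mixing the two terms in the RED sentence as well means that a reader cannot be sure which was intended.

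**Recruitment is assessed elsewhere.** This stands. Consents and declines are recorded as a primary feasibility outcome. Data analysis of primary outcomes tabulates referrals, consent-to-contact and informed consent. A numerical target of 32 is given. A reader might infer from the GREEN sentence that poor recruitment would go unseen, but the documents do not support that: 10 consents would be reported against a plan of 32. What is missing is any statement that these counts qualify a GREEN result.

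**The rule does not mislead in both directions.** This also stands. A reader might infer that RED condemns a study that recruited well. RED asks only for better retention, and AMBER says only that the methodology may need amending.

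**The colours are advisory.** A reader might take GREEN as proof of feasibility, or as an automatic decision to proceed. The text says only that GREEN will indicate feasibility, and it binds no future trial to the colour. That limits the harm but does not make the indication valid.

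**An article may leave further criteria to a fuller document.** That would answer a complaint that a recruitment criterion is absent. It does not answer a complaint about a conclusion that the article states and that does not follow.

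**Conclusion.** The point holds for the GREEN sentence. Retention among consented participants cannot show that a methodology is feasible for recruitment, and the article's own objectives, outcomes and Discussion treat recruitment as a separate question. The size is best expressed as a range: GREEN, with its recruitment conclusion, is compatible with any level of recruitment. With 9 of 10 retained, it would be given at 31% of the planned 32.

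The consequence is a wrong label on a leading aim. No data are concealed, and no estimate or participant is affected. The conclusion rests on the article's definition of retention and on there being no other progression criterion in it. The sentence would remain wrong even if a fuller protocol held a recruitment criterion.

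**What to change.** In Sample size consideration:

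1. Restrict the GREEN, AMBER and RED conclusions to retention. GREEN would say that the methodology is feasible for participant retention, and RED that considerable changes are needed to improve the retention of recruited participants.
2. State that feasibility of recruitment is judged separately from data already to be collected: the number consented against the planned 32, and the number consented out of eligible service users approached. Name the denominator, because the research team assesses eligibility only after consent-to-contact.
3. Choose one of two courses and say which. If a numerical recruitment threshold is added, date it and declare it as added during recruitment, since recruitment began in November 2023. If none is added, say that recruitment is judged descriptively and that a GREEN result does not cover it.

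Item 1 is a pure wording correction. Item 2 uses counts already planned under Primary feasibility and acceptability outcomes and Data analysis of primary outcomes. A threshold under item 3 would be a small design decision. A formal two-colour rule is not needed to cure the defect. The downside is that the overall feasibility message may be less favourable than a GREEN retention rate alone would suggest.

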#### Data analysis of primary outcomes

The focus will be on tabulated and associated graphical summaries of the key indicators associated with the outcomes of a feasibility trial, which includes participant recruitment and attendance. Specifically, summary statistics will be the total number of referrals to the P-CFT groups, the number of service users who provide consent-to-contact and the number of service-users who provide their informed consent. Furthermore, group attendance and dropout rates, completion of follow-up outcome data and the number of participants who are retained at each timepoint will also be generated.

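### The retention colour is worded as a conclusion, but at n = 32 it cannot reliably separate adjacent bands near a cut-off

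*Protocol article*

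**What the plan says.** All of the rule is in the protocol article, Component 1, Sample size consideration.

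- **Size.** No formal calculation was made. The text says: "It is planned to recruit 50% of this potential pool of participants (*n* = 32), approximately ten to 11 participants per site for baseline recruitment".
- **Bands.** They read "a retention rate above 85% will be considered acceptable (GREEN), 65% to 84% will be considered a borderline level of retention (AMBER"), with RED for anything below 65%.
- **Conclusions.** GREEN *will indicate* that the methodology is feasible. For AMBER the wording is hedged: amendments *may be required*. For RED it is firm: "A retention rate of RED demonstrates that considerable changes would be necessary to improve retention of participant recruitment".

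Primary feasibility and acceptability outcomes defines retention as the consented participants still in Component 1, at both post-intervention and follow-up. Data analysis of primary outcomes describes tabulated and graphical summaries and adds that "the number of participants who are retained at each timepoint will also be generated". None of these sections gives an interval, a precision statement or an error rate for the retention rate.

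**The concern.** The rule, on its natural reading, compares the observed percentage with fixed cut-offs, and the text then treats the colour as a finding. With 32 people, one person is 3.1 percentage points (1/32), so a change of one or two people near a cut-off changes the colour. The colour is tied to whether future P-CFT studies keep the methodology, amend it or change it considerably. A study with borderline retention could be reported as feasible, or one with adequate retention sent for amendment, and the reader would not see how close the call was. The cautious phrasing used for AMBER shows that similar wording was available for GREEN and RED.

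**Working it through.** **1. The plan's own figure.** The article states that "the potential pool of participants is 64 to 128 participants" and plans to recruit half: 0.5 × 64 = 32, which reproduces n = 32 from the lower end of the pool. (The article also says "approximately 17 groups will be offered across three NHS trusts"; 17 × 4 = 68, half of which is 34. Step 6 shows what that changes.)

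**2. Cut-offs as counts at n = 32.**
- GREEN: 0.85 × 32 = 27.2, so 28 or more retained.
- RED: 0.65 × 32 = 20.8, so 20 or fewer.
- AMBER: 0.84 × 32 = 26.88, so 21 to 26.
- 27/32 = 84.4% lies in neither the GREEN nor the AMBER band as printed.

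**3. Precision.** The Clopper-Pearson 95% limits for x retained of n are the 2.5% point of Beta(x, n − x + 1) and the 97.5% point of Beta(x + 1, n − x).

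| Retained | Observed | Exact 95% interval |
|---|---|---|
| 20/32 (highest RED) | 62.5% | 43.7% to 78.9% |
| 22/32 | 68.8% | 50.0% to 83.9% |
| 23/32 | 71.9% | 53.3% to 86.3% |
| 26/32 | 81.3% | 63.6% to 92.8% |
| 27/32 (unclassified) | 84.4% | 67.2% to 94.7% |
| 28/32 (lowest GREEN) | 87.5% | 71.0% to 96.5% |
| 31/32 | 96.9% | 83.8% to 99.9% |

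The intervals at both edge counts reach well into AMBER.

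**4. Error rates.** The true rates below are assumptions, because the article gives no expected retention. With X ~ Binomial(32, p) and independent participants, P(GREEN) = P(X ≥ 28) and P(RED) = P(X ≤ 20).

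| True rate (assumed) | Error | Probability | If 27/32 counts as GREEN |
|---|---|---|---|
| 60% (RED) | not called RED | 32.3% | unchanged |
| 70% (AMBER) | called RED | 22.8% | unchanged |
| 75% (AMBER) | called RED | 8.0% | unchanged |
| 75% (AMBER) | called GREEN | 7.0% | 15.3% |
| 80% (AMBER) | called GREEN | 20.4% | 36.0% |
| 84% (AMBER) | called GREEN | 40.3% | 59.3% |
| 88% (GREEN) | not called GREEN | 33.8% | 17.9% |
| 90% (GREEN) | not called GREEN | 21.1% | 9.4% |
| 95% (GREEN) | not called GREEN | 2.0% | 0.5% |

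Averaged evenly over the band, AMBER (taken as 65% to 85%) is called GREEN 12.5% of the time, and GREEN (85% to 100%) is missed 15.8% of the time, with 27/32 counted as not GREEN.

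**5. Opposite colours.** P(GREEN) at a true 65% is 0.4%, and P(RED) at a true 85% is about 0.2%. The rule does separate RED from GREEN.

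**6. Other sample sizes.** The three errors are a true 80% called GREEN, a true 90% missing GREEN and a true 70% called RED. At n = 34 they are 30.0%, 11.9% and 30.7%. At n = 64 (half of 128) they are 15.0%, 10.3% and 18.3%, with the unclassified 54/64 counted as not GREEN. The size of each error depends on where the whole-number cut-off falls, but none of them disappears.

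**The case against.** Point-estimate progression criteria are common in feasibility studies, and this one disclaims formal sizing. An interval for a descriptive proportion may be in a full protocol or analysis plan that is not shown, and the planned summaries do not exclude one. The cited framework for the traffic light cannot be consulted. GREEN only *will indicate*, and what RED is said to demonstrate is a need for changes, not that true retention lies below 65%. Retention is also read alongside recruitment, attendance, questionnaire completion and the interviews, and no binding stop/go decision hangs on the colour.

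Most of this stands. It rules out four stronger readings that a reader might infer:

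- *The missing interval is itself an error.* An article may leave it to another document. The fault is in the printed wording, which is stronger than 32 people can support.
- *The colour is wrong about one time in five.* That holds only near assumed true rates of 80% and 90%. An error near one half at a cut-off would occur at almost any sample size.
- *The rule cannot tell its bands apart.* It fails for adjacent bands near a cut-off, not for RED against GREEN.
- *GREEN should require a lower limit above 85%.* Only 32/32 would pass (lower limit 89.1%). That is a confirmatory standard which the study does not claim to meet.

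Rounding to whole percentages would place 27/32 in AMBER at 84%, but the article states no rounding rule. What survives the objection is the firm wording for RED and GREEN and the gap between the bands.

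**Conclusion.** The concern holds in a limited form. At n = 32 the colour is a rough indicator near a cut-off, and the text presents it as a conclusion. Misclassification into an adjacent band is about 20% to 23% at true rates of 70%, 80% and 90%. It is larger closer to a cut-off and smaller further away. The two figures at the upper cut-off depend on how 27/32 is treated.

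The interval would still say something useful. At 27 or more retained it excludes the RED band (lower limit 67.2% or higher), and at 22 or fewer it excludes GREEN (upper limit 83.9% or lower).

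The calculations assume 32 recruited and independent outcomes. Participants are treated in groups of four to eight, and dropout that clusters by group would widen the intervals by an amount the article gives no basis to quantify. This is a minor to moderate point about what the study may claim. It does not affect its design or size.

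**What to change.** Keep n = 32 and make three changes:

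1. Make the bands contiguous so that every count has a colour. For example, AMBER could run from 65% up to but not including 85%, with GREEN from 85%; this puts 27/32 in AMBER. The choice is the authors', but it should be made before the data are seen.
2. Report retention at post-intervention and at follow-up, each with its exact (Clopper-Pearson) 95% interval beside the colour, and say which bands the interval excludes.
3. Replace *will indicate* and *demonstrates* with wording that the colour is provisional where the interval crosses a cut-off and is read together with the other feasibility outcomes.

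If error rates are to be printed as well, the gap between the bands must be closed first, because they depend on it.

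The cost is a few sentences and one table column, with no extra participants or data. The downside is a less clear-cut feasibility statement: of the counts from 18 to 32, only 32/32 has an interval clear of both cut-offs, so most results would be labelled provisional.
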